##### Severe reactions

2.9.5.2

Hot compresses can alleviate pain in the needling points.Local redness, swelling, pain, fever, and other inflammatory manifestations caused by secondary infection can be resolved within 3–4 days.Nerve injury can occur due to incorrect operation, over-stimulation, or carelessness but can be prevented carefully.Bleeding may happen because of puncturing blood vessels or excessive stimulation. Compression bandages can be used to stop bleeding.Local itching, redness, swelling, fever, etc., may be symptoms of an allergy to threads. Anti-allergic treatment can be given in such cases.

Appropriate actions are taken to address more severe reactions in accordance with the grading and management of adverse reactions in CEA (37). Effective measures include discontinuation of the trial or ethically appropriate additional mechanisms.

### Outcome measurement: primary outcomes

2.10

#### BMD test

2.10.1

The patient’s BMD of L2-L4 in the lumbar spine and BMD of the left femoral neck will be measured by DXA once before and after the treatment.

#### Total efficiency of Chinese medicine symptoms

2.10.2

According to the “Guidelines for Clinical Research on New Chinese Medicine,” the efficacy assessment criteria for osteoporosis are as follows:

Significant efficacy: bone density examination shows an increase in bone density.

Effective: significant relief of pain, and bone density examination shows no decrease in bone density.

Ineffective: no improvement in all aspects compared to before treatment.

The efficacy index is calculated by integrating the scores before and after treatment, where the efficacy index = (score after treatment-score before treatment) / score before treatment × 100%.

The overall effective rate = (significant efficacy + effective) /*n* × 100%.

### Outcome measurement: secondary outcomes

2.11

#### Clinical manifestation

2.11.1

SF-MPQ and OSS will be measured every four weeks for 5 months. All evaluation indicators will be assessed at six time points: baseline, mid-treatment (4 and 8 weeks of treatment), post-treatment (12 weeks), and 1 month and 2 months after the treatments.

##### SF-MPQ

2.11.1.1

The first part of the SF-MPQ consists of 15 pain descriptors, of which 11 are items about self-sense and four are about uncomfortable feelings. Each item has three levels, from 0 (painless) to 3 (severe) (Table 4).

**Table 4 tab4:** Short-form McGill Pain Questionnaire Part I.

	Pain Rating Index	None (0)	Light (1)	Medium (2)	Heavy (3)
Sensory rating	Throbbing pain				
	Piercing				
	Stabbing pain				
	Sharp pain				
	Cramping pain				
	Colic				
	Hot-burning pain				
	Continuous fixation pain				
	Swelling and pain				
	Pain caused by light touch				
	Splitting pain				
Emotional rating	Tiring-exhausting				
	Sickening				
	Fearful				
	Punishing-cruel				

The second part is a 10-centimeters-long visual assessment scale (VAS), marked as “painless” at one end and “intolerable pain” at the other end, on which the participants draw the level of pain (Figure 2).

**Figure 2 fig2:**

The VAS scale.

The third part is the present pain level (PPI), generally used to indicate pain intensity on a scale. The Scale has five levels, from 0 (painless) to 5 (intolerable pain). PMOP patients were evaluated before and after treatment, including the current pain and how pain has been felt in the past week (Table 5).

**Table 5 tab5:** Present pain intensity.

Pain Level	Description of pain intensity
0	Painless
1	Mild pain (occasionally annoying due to pain)
2	Moderate pain (often annoying but tolerable with restraint)
3	Severe pain (can only tolerate partial pain)
4	Terrible pain (severe pain, often causing moaning)
5	Unbearable pain (feeling the pain too much to commit suicide)

##### OSS

2.11.1.2

According to the quantitative criteria for grading the significant clinical symptoms of OP in the “Technical Guidelines for Clinical Studies on New Chinese Medicines for Primary Osteoporosis.” The subjects are assessed on a scale according to time points (Table 6).

**Table 6 tab6:** Quantitative criteria for clinical main symptom grading of OP.

Symptom	Light (score 1 points)	Medium (score 2 points)	Heavy (score 3 points)
Pain in the lower back***	1 ~ 3 degree	4 ~ 6 degree	7 ~ 10 degree
Soreness and weakness of waist and knees**	Occur after walking over 1 km	Occur after walking 300 ~ 1 km	Occur after walking under 300 m
Leg cramps**	Occur occasionally at night	Occur frequently at night	Occur frequently at day and night
Trudge*	Short-distance walking without discomfort within 100 m	Difficulty in walking short distances (10–100 meters)	Difficulty in walking (unable to exceed 10 m), or standing
Sedentary difficulty*	Less power to hold heavy	The intermediate state	Completely no power to hold heavy

① Pain level can generally be assessed by the VAS pain scale method; ② *** means score x 3; ** means score x 2; * means score x 1; ③ Subjects use diary cards to record symptoms, and the doctor communicates with the subjects after evaluation.

#### Clinical objective indicators

2.11.2

The secondary outcome measures are (i) Leptin, (ii) Leptin Receptor (iii) Noradrenaline. The leptin, leptin receptor, and norepinephrine levels of peripheral blood must be measured before and after treatment.

Blood samples should be collected on the day of entry and the first day after the end of treatment for the CEA group, the rTMS group, and the CEA combined with rTMS group. Before sampling, all required tubes should be prepared and appropriately labeled with the study protocol number, subject number, study phase, period, and date and time of sampling. The authorized research nurse is responsible for collecting the blood specimens. After collection, the tubes are inverted and mixed. Blood is drawn in the order required by the collection process to prevent cross-contamination between different types of boxes. If a tube is contaminated, it should be replaced immediately with a spare tube and re-labeled. Vital signs are recorded before sampling. Blood is drawn from a venous elbow at 8:00 am in the fasting state. 3 mL of blood is collected in a pre-prepared tube, and after being centrifuged, the serum is collected for testing. 5 mL of blood is contained in a pre-prepared anticoagulation tube (20 μL/mL of peptidase, 20 μL/mL of 10% EDTA-Na2), centrifuged, and plasma collected for testing. Collect 5 mL of blood in a pre-prepared anticoagulation tube (20 μL of peptidase, 20 μL of 10% EDTA-Na2); after being centrifuged, the plasma is collected for testing.

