#### The CEA group

2.9.2

Our treatment method is based on previous literature reports (30).

The treatment group will undergo 12 weekly sessions of CEA for 3 months. The primary acupoints will be BL23, SP6, and RN4, with additional acupoints like BLI8, GB39, BL11, BL20, and ST36 added, depending on whether the case is a liver-kidney deficiency or kidney yang deficiency. During each treatment, RN4 is essential, while the other acupoints can be alternated between the left and right sides. The acupoint location method will follow the State Bureau of Technology Supervision standards. In addition, the operating procedure will be based on the National Standards of GB/T 21709.10–2008 manipulations of acupuncture and moxibustion, Part 10 Acupoint catgut embedding. Detailed information about the intervention group and acupoint location can be found in Tables 2, 3 of the STRICT checklist for reporting interventions in clinical acupuncture trials (Tables 2, 3).

**Table 2 tab2:** Acupoints selection.

Primary point	Additional point	
	Deficiency of liver and kidney	Deficiency of kidney yin
Shenshu (BL23) Sanyinjiao (SP6) Guanyuan (RN4)	Dazhu (BL11) Ganshu (BL18)	Xuanzhong (GB39) Zusanli (ST36) Pishu (BL20)

**Table 3 tab3:** Acupoints location.

Point	Location
BL23	1.5 cun lateral to the depression below the spinous process of the second lumbar vertebra
SP6	Posterior to the mesial border of the tibia and 3 cun above the tip of the medial malleolus
RN4	On the anterior midline, 3 cun below the umbilicus
BL18	1.5 cun lateral to the depression below the spinous process of the 9th thoracic vertebra
BL11	1.5 cun lateral to the lower border of the spinous process of the first thoracic vertebra
GB39	3 cun above the tip of the external malleolus, on the anterior border of the fibula
ST36	3 cun directly below Dubi (the lateral depression of the knee-joint) and one middle finger-breadth lateral to the anterior border of the tibia
BL20	1.5 cun lateral to the depression below the spinous process of the 11th thoracic vertebra

Cun=an acupuncture measurement unit; 1 cun corresponds to the study subject’s thumb width.

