#### The rTMS group

2.9.3

The treatment will be completed by a trained professional therapist using a transcranial magnetic stimulator (YRD CCY-II from Wuhan Eredo). The motor threshold (MT) and dorsolateral frontal lobe (DLPFC) stimulation site are to be determined during the first treatment. The room temperature will be maintained at 16°C–23°C, and the patient will be lying flat on their side on the treatment bed. The motor-evoked potentials (MEPs) are to be recorded in the contralateral hand’s interosseous muscle through the magnetic stimulator’s electromyographic amplifier, with the center of the “8” coil placed on the right temporal cortex of the subject. The stimulation site and the stimulation volume are adjusted until at least 5 out of 10 stimulations evoke MEPs with an amplitude more significant than 50 μV, at which point the magnetic flux is MT, and move 4 cm forward horizontally at the site where the MEPs are elicited, which is the DLPFC. We plan to utilize a positioning cap and a transcranial magnetic stimulator (YRD CCY-II from Wuhan Iredell) to accurately identify and target the specific location during the procedure (31). We intend to choose the right DLPFC point as the stimulation site. The stimulation intensity will be set at 80% of the resting movement threshold, with a frequency of 1 Hz, lasting 30s with an interval of 4 s, and 10 series to be performed continuously on the patient (32, 33). The treatment plan will consist of one session per day, 5 days a week, for 4 weeks (34, 35). Starting from the fifth week, the treatment plan changes to twice a week for eight consecutive weeks (36). In total, this treatment plan will last for 12 weeks and include 36 sessions.

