#### The CEA combined with rTMS group

2.9.4

Subjects in this group will receive both the CEA and the rTMS treatment according to the respective regimens of the two therapies.

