##### Mild reactions

2.9.5.1

Local aseptic inflammatory reactions, such as redness, swelling, heat, and pain, often occur within 1–5 days.Systemic reactions may include a rise in body temperature within 4–24 h after treatment and an increase in blood count, which usually returns to normal in 3–5 days.

Most of the mild reactions are physiological after the treatment, do not need to be treated, and can be relieved on their own within a short period.

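### The single post-treatment biomarker draw has no set interval from the last catgut embedding, so it can fall inside the protocol's own post-procedure reaction period in the two CEA-containing arms only

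*Protocol article*

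**What the plan says.** - **Sampling.** Section 2.11.2 applies one rule to all three arms: "Blood samples should be collected on the day of entry and the first day after the end of treatment". It also fixes a fasting draw at 8:00 am. Table 1 shows blood collection and the three markers at weeks 0 and 12 only, so there is one post-treatment sample.
- **CEA.** Section 2.9.2: "The treatment group will undergo 12 weekly sessions of CEA for 3 months".
- **rTMS.** Section 2.9.3 gives five sessions a week for four weeks, then: "Starting from the fifth week, the treatment plan changes to twice a week for eight consecutive weeks". It closes: "In total, this treatment plan will last for 12 weeks and include 36 sessions".
- **Combined arm.** Section 2.9.4: "Subjects in this group will receive both the CEA and the rTMS treatment according to the respective regimens of the two therapies". Two of the three arms therefore receive embeddings.
- **Expected reactions.** Section 2.9.5.1: "Local aseptic inflammatory reactions, such as redness, swelling, heat, and pain, often occur within 1–5 days". It continues: "Systemic reactions may include a rise in body temperature within 4–24 h after treatment and an increase in blood count, which usually returns to normal" in 3 to 5 days. The section does not name CEA. The neighbouring section 2.9.5.2, on needling points, thread allergy and the grading of CEA reactions, makes that the sensible reading.
- **Completion window.** Section 2.5 uses 12 weeks plus or minus 5 days.

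**The concern.** Leptin, leptin receptor and norepinephrine are the trial's only blood markers of mechanism, and mechanism is a stated aim (Introduction; section 3.4). Section 3.4 predicts lower leptin and norepinephrine after the combined therapy. If the post-treatment sample is taken while pain, local inflammation or a systemic reaction to the last embedding may still be present, a before-after change could mix a short procedural response with the effect of the course.

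The exposure depends on the assigned arm. CEA-treated patients can be sampled within the reaction period, and patients on rTMS alone cannot, because they have no embedding. Randomisation does not balance something that the assigned treatment creates. The interval can also differ between the CEA and combined arms. With no later blood sample, the data could not separate the two explanations.

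**Working it through.** The plan states no figure on this point, so there is none to reproduce. The check is a count of days from the last embedding to the draw under the two possible meanings of the end of treatment.

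**Inputs.** CEA: 12 weekly sessions (2.9.2). rTMS in weeks 5 to 12: twice weekly (2.9.3). The rTMS total agrees with its schedule: 5 × 4 + 2 × 8 = 36. Reaction periods: 1 to 5 days local, and 3 to 5 days until systemic reactions usually settle (2.9.5.1).

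**Reading A: the draw is the day after the last session.**
- CEA arm: the gap is 1 day. With an 8:00 am draw, an embedding done after 8:00 am on the previous day is less than 24 hours old, so the draw can also fall in the 4 to 24 hour period given for a temperature rise.
- Combined arm: suppose (my assumption) that week-12 sessions fall on weekdays 1 to 5, with CEA on weekday c and the last rTMS session on weekday r. As there are two rTMS sessions that week, r is at least 2. Gap = max(c, r) + 1 − c.
  - c = 1, r = 5: 5 + 1 − 1 = 5 days.
  - c = 3, r = 5: 5 + 1 − 3 = 3 days.
  - c = 5, any r: 5 + 1 − 5 = 1 day.
  - Range: 1 to 5 days.
- rTMS arm: no embedding, so no such exposure.

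Every gap in the two CEA-containing arms is 5 days or less.

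**Reading B: the draw is on day 85, after an 84-day course.** If the first CEA session is on day f, the twelfth is on day f + 7 × 11 = f + 77, and the gap is 85 − (f + 77) = 8 − f.

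| First CEA on day | Twelfth CEA on day | Gap to day 85 |
|---|---|---|
| 1 | 78 | 7 |
| 2 | 79 | 6 |
| 3 | 80 | 5 |
| 4 | 81 | 4 |
| 5 | 82 | 3 |
| 6 | 83 | 2 |
| 7 | 84 | 1 |

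The draw clears 5 days only when CEA starts on day 1 or 2.

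**What a shift would do, if there were one.** The documents give no marker response, so the shifts here are assumptions. Take 32 per arm, no true treatment difference, and a mean shift of d standard deviations in the CEA arm only. A two-sided 5% t-test against the rTMS arm (df = 62) then has noncentrality d × √(32/2) = 4d:
- d = 0.2: noncentrality 0.8, rejection 12.4%.
- d = 0.3: noncentrality 1.2, rejection 21.9%.
- d = 0.5: noncentrality 2.0, rejection 50.4%.

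This shows how sensitive the comparison would be. It does not estimate the bias in this trial.

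**The case against.** The strongest reply is that the text does not say one day after the last session. A reader might infer that every CEA-arm sample is certainly drawn on the first day of the reaction period. The documents do not support that: the end of treatment is undefined, and under the 84-day reading the gap can reach 7 days. This objection stands. It does not remove the problem, because under that reading the gap still runs from 1 to 7 days, and nothing in the article constrains it or asks for it to be recorded.

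Second, a reader might infer that the draw does pick up acute procedure effects. Section 2.9.5.1 says only that systemic reactions may occur, describes most mild reactions as physiological and self-limiting, and mentions none of the three markers. That stands too: what can be shown is an overlap in timing, not a bias. The assumed shifts above also move a whole arm's mean, whereas the section describes reactions that only some patients may have.

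Third, the Introduction presents the absorbable thread as a means of sustained stimulation, so a local response could count as part of the treatment. Section 3.4 does not require the predicted marker changes to be lasting. An end-of-course draw is therefore defensible in principle. What is hard to defend is an interval from the last embedding that is left open and can differ between arms.

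**Conclusion.** The point holds as a risk of confounding in a secondary comparison. On the natural reading, the stated sampling day falls 1 day after embedding in the CEA arm and about 1 to 5 days after it in the combined arm, with no corresponding exposure under rTMS alone. On the alternative reading, the gap is 1 to 7 days and depends on scheduling. These counts rest on weekly CEA, weekday sessions in week 12 for the combined arm, and attributing the section 2.9.5.1 reactions to CEA.

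The existence, direction and size of any effect on leptin, leptin receptor or norepinephrine cannot be taken from the documents. Neither bone mineral density nor the total efficiency of Chinese medicine symptoms depends on this draw, so a reader should not extend the point to the primary outcomes. The change is worth making because it is cheap and the only post-treatment sample cannot be repeated.

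**What to change.** In section 2.11.2, replace the current post-treatment timing with one common study day for all three arms, chosen to be more than 5 days after the last embedding in both CEA-containing arms. Use the same study day in the rTMS arm. For example, where weekly CEA starts on day 1, day 85 is 7 days after the twelfth session. It also lies inside the completion window, which runs from day 84 − 5 = 79 to day 84 + 5 = 89. Anchoring to a study day is better than counting from the last session of either kind, which would leave the embedding-to-draw gap unequal whenever rTMS finishes last. Keep the 8:00 am fasting rule, and record on the case report form the days since the last CEA session and since the last rTMS session.

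The cost is a wording change and possibly a blood draw scheduled apart from the last session. A very short-lived post-session response would no longer be captured. Treatment schedules are unchanged.

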### Measures to prevent excessive loss of cases

2.12

Communicate in detail with patients about the trial process, provide adequate information, clarify their responsibilities and obligations and the importance of the trial, and sign the informed consent form.Simplify the trial process as much as possible to reduce the burden on subjects. Reasonably arrange the time for data collection and treatment of subjects.Actively respond to patients’ feedback during treatment to improve patient compliance.Develop standard operating procedures for data collection and measurement of subjective and objective indicators and strengthen training for investigators in data collection, communication skills, and scoring operations, which can improve patient compliance and reduce the incidence of missing data.Establish a comprehensive case tracking system to ensure that case participation and follow-up can be effectively managed and recorded.

### Safety assessment

2.13

Current studies about rTMS have shown few side effects. Given that this study is a low-risk intervention, small sample clinical mechanism research trial, there is no need for a dedicated data safety and monitoring committee. To ensure the rights of participants and the smooth running of the trial, we have developed a data safety and monitoring plan based on the specificity of the disease, subject population, interventions, and outcome indicators of the study. After review by the Ethics Committee, safety inspectors are appointed to track, record, report, and deal with adverse events.

Therapists need to follow the CEA process strictly to ensure the concept of sterility and safety. Comply with the graded treatment of adverse reactions to CEA, assess and effectively identify the grade of adverse reactions in patients promptly, reduce the occurrence of adverse reactions and attenuate their harm, and deal with them promptly (37). Strictly exclude contraindications to rTMS treatment, sign an informed consent form, and complete a safety screening assessment. We intend to select the intensity, frequency, and number of rTMS stimulations according to the treatment purpose since the individual differences in resting motor threshold (RMT) determination. It should be strictly limited to safe sequences and avoid sequences that induce seizures and other risks. The assessment and effective management of adverse effects during treatment should be strictly controlled. Although the current rTMS treatment has a low risk, it is still necessary to prevent rTMS-induced seizures. It has been reported that rTMS can induce seizures in both standard and epileptic patients when the stimulation frequency is between 10 and 25 Hz and the stimulation intensity is above the threshold (38). For example, if a patient experiences a seizure, treatment should be stopped immediately, and first aid should be administered. Application of rTMS near the affected ear should be avoided in patients with hearing symptoms (e.g., tinnitus or phantom hearing).

### Statistical analysis

2.14

The data will be recorded and checked for accuracy, and the data related to baseline and clinical symptoms will be statistically analyzed using SPSS 27.0 software. The *t*-test will be performed for customarily distributed measures that meet the chi-squared test, and the *t′*test will be conducted for standards that meet the normal distribution but do not meet the chi-squared test. Independent sample *t*-tests are used between two groups, and paired sample *t*-tests will be used for pre-treatment and post-treatment comparisons within groups. Non-normally distributed measures are described by “median (interquartile range)” [*M (IQR)*], and non-parametric tests will be performed. *The Mann–Whitney U* test will compare two independent samples, and the *Wilcoxon Z* test will be used for pre-and post-treatment-comparisons. The scale scores at more than three of these time points are compared using repeated measures *ANOVA*. Correlations will be expressed as correlation coefficients (*r*). Correlations between the two measurement variables will be analyzed by Pearson correlation analysis if they conform to a normal distribution and Spearman analysis if they do not obey a normal distribution. Given that our study defines two primary outcomes, a Bonferroni correction will be applied, thus adjusting the significance level for individual outcome analyzes to *α*/2 to control the overall type I error rate, setting *α* = 0.05 (39).

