**Method:**

This trial is a prospective and randomized controlled trial. 96 PMOP participants will be randomized in a 1:1:1 ratio into a CEA group, an rTMS group, or a combined one. Participants will receive CEA, rTMS, or combined therapy for 3 months with 8 weeks of follow-up. The primary outcomes will be the changes in Bone Mineral Density scores, total efficiency of Chinese Medicine Symptoms before and after treatment. Secondary outcomes include the McGill Pain Questionnaire Short-Form, Osteoporosis Symptom Score, Mini-Mental State Examination, and Beck Depression Inventory-II. The leptin, leptin receptor, and norepinephrine levels of peripheral blood must be measured before and after treatment. Adverse events that occur during the trial will be recorded.

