Repetitive transcranial magnetic stimulation (rTMS) generates a robust and rapidly changing magnetic field that induces current in the target area under the coil, thus activating cortical and subcortical neurons. It regulates neuronal excitability or inhibition, evaluates the corticospinal tract, and enhances brain plasticity (19, 20). This technique has been applied to evaluate the motor system, explore brain function, and investigate the pathophysiology of psychiatric disorders (21, 22). rTMS is currently an essential neuromodulation technique that can be used directly by stimulating the central targets in order to treat neurological diseases and peripheral systemic conditions (23, 24). Based on the neuro-bone mass regulation theory, we propose a central stimulation intervention to regulate bone metabolism by using the neuromodulatory effect of rTMS. We hypothesize that the combination of CEA and rTMS may have a coordinated, synergistic, and reaction-reduced effect, which has significant clinical value in exploring better treatment options for PMOP. The prevention and treatment of PMOP should not rely solely on peripheral interventions but also focus on central involvement. It is essential to integrate central and peripheral regulation for bone remodeling with the participation of the central and peripheral nervous systems.

CEA achieves brain bone mass regulation through the bottom-up peripheral-central way, while rTMS achieves it through the top-down stimulation of the central-peripheral (25). The combination of CEA and rTMS may achieve a bidirectional central-peripheral intervention on bone metabolism (26). Consequently, the study aims to explore the clinical effectiveness and safety of rTMS combined with CEA in treating PMOP from the perspective of central-peripheral regulation. We would like to preliminarily investigate the intrinsic correlation between CEA combined with rTMS, brain bone mass regulation, and clinical signs and elucidate the central mechanism of CEA combined with rTMS in regulating bone metabolism.

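### BMD and blood markers are compared between arms without baseline adjustment, and that comparison is not made primary over within-arm pre/post tests, which cannot show efficacy in three active arms

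*Protocol article*

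**What the plan says.** Participants are "randomized in a 1:1:1 ratio into a CEA group, an rTMS group, or a combined one" (Abstract, Method). All three arms are active, and section 2.9 gives one calcium and vitamin D regimen for the whole trial. BMD "will be measured by DXA once before and after the treatment" (section 2.10.1). Leptin, leptin receptor and norepinephrine are also taken before and after treatment (section 2.11.2 and Table 1), so a baseline value exists for each.

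Section 2.14 sets the tests:

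- Between arms: independent-sample t, t′ or Mann-Whitney tests. The key words are "tests are used between two groups, and paired sample". No covariate is named.
- Within arms: paired t-tests, or Wilcoxon tests if non-normal. The paired t-tests "will be used for pre-treatment and post-treatment comparisons within groups".
- The t-test is reserved for "customarily distributed measures that meet the chi-squared test"; normal measures that fail that check go to t′.
- Scales with many visits: "The scale scores at more than three of these time points are compared using repeated measures" ANOVA.

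The section does not say which of these is the primary efficacy comparison, nor whether the two-sample test on BMD is run on the change or on the final value. The Abstract states: "The primary outcomes will be the changes in Bone Mineral Density scores, total efficiency of Chinese Medicine Symptoms before and after treatment". The Introduction puts forward the hypothesis that "the combination of CEA and rTMS may have a coordinated, synergistic, and reaction-reduced effect".

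**The concern.** Two things are at stake.

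The first is precision. A two-sample test on BMD or a blood marker leaves the baseline value either unused or used only through subtraction. ANCOVA uses it optimally, at no cost in patients or visits.

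The second is interpretation. A pre/post test within one arm measures everything that happened between the two visits: treatment, passage of time, the shared supplements and regression to the mean. The last is a concrete risk, because patients enter on a diagnosis based on low DXA readings (section 2.3). No arm lacks active treatment, so nothing in the design separates these components. The invitation to misread is there: the primary outcomes are framed as changes before and after treatment, and section 2.10.2 grades each patient against her own pre-treatment state. If the paired tests stand level with the between-arm tests, three significant p-values could be reported as three effective treatments while the randomised comparison shows nothing.

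**Working it through.** **1. The plan's own figure.** Section 2.14 gives no precision figure. The nearest is in section 2.8: N = 87 from a one-way ANOVA at two-sided α 0.05 and power 0.95. The inputs are decreases in SF-MPQ of 17.23 ± 2.84 (CEA), 16.41 ± 1.77 (rTMS) and 17.40 ± 2.17 (combined).

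- SD of the arm means: √[(0.217² + 0.603² + 0.387²)/3] = 0.432
- Pooled SD: √[(2.84² + 1.77² + 2.17²)/3] = 2.303
- f = 0.432/2.303 = 0.188
- Noncentral F with λ = N·f²: 95% power needs N = 444, and N = 87 gives power 0.32.

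So 87 does not reproduce. That is a separate point; here it shows only that precision is not in surplus.

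**2. What baseline adjustment saves.** Let the SDs before and after treatment be equal (σ) and the correlation r. The variances per patient are σ² for the final value, 2σ²(1 − r) for the change and σ²(1 − r²) for ANCOVA. ANCOVA relative to change is therefore (1 − r²)/[2(1 − r)] = (1 + r)/2. The document gives no r, so a range is assumed.

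| r | ANCOVA / change | ANCOVA / final value |
|---|---|---|
| 0.3 | 0.65 | 0.91 |
| 0.5 | 0.75 | 0.75 |
| 0.7 | 0.85 | 0.51 |
| 0.9 | 0.95 | 0.19 |

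**3. What that does to power.** The pilot SDs are SDs of change. Applying (1 + r)/2 to their variance moves three-arm power at N = 87 from 0.32 to 0.46, 0.41, 0.37 and 0.33 for the four values of r. The N for 95% power falls from 444 to 288, 333, 378 and 420. This is a gain, but not a rescue.

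**4. Within-arm against between-arm, on the pilot SF-MPQ figures.** Take 87/3 = 29 per arm. The paired t is mean/(SD/√29):

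- CEA: 17.23/0.527 = 32.7
- rTMS: 16.41/0.329 = 49.9
- Combined: 17.40/0.403 = 43.2

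With 32 per arm the values are 34.3, 52.4 and 45.4. Between arms, the standard error is 2.303 × √(2/29) = 0.605:

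- Combined minus rTMS: 0.99 points, t = 0.99/0.605 = 1.64, power 0.37
- Combined minus CEA: 0.17 points, t = 0.17/0.605 = 0.28, power about 0.05

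The paired tests are overwhelming in every arm and carry no information on which arm is better.

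**5. Synergy.** On the additive scale, synergy is combined − CEA − rTMS + neither. With the pilot decreases this is 17.40 − 17.23 − 16.41 + D₀ = D₀ − 16.24, where D₀ is the mean decrease with neither treatment. The sign depends wholly on D₀, which the trial does not observe.

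**The case against.** The strongest reply has five parts.

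*The unadjusted tests are valid.* This stands. Under randomisation a two-sample test is a sound comparison. A reader might infer that only an adjusted model is legitimate, but the loss is in precision alone. Against change scores it shrinks to 5% of the variance at r = 0.9. Since the BMD outcome is defined as a change, the final-value column may not apply to it.

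*The document does not say that efficacy will be judged from the paired tests.* This also stands. Section 2.14 lists them beside between-arm tests, section 2.1 states a comparison of three groups, and section 2.8 sizes the trial on a three-group ANOVA. A reader might infer from the before-and-after wording that the paired tests decide; the text does not go that far. The fault is that it does not rank them.

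*The scales do not get plain two-sample tests.* Correct. SF-MPQ, OSS, MMSE and BDI-II, with six time points, go to repeated measures ANOVA, which includes the baseline visit. The precision argument therefore falls on BMD and the blood markers. The paired t values above come from SF-MPQ and illustrate the logic; the document gives no pilot BMD or marker changes from which to claim the same there.

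*The chi-squared wording is a slip.* Evidently: the branch to t′ shows that equality of variances is meant. It still needs correction, since no such check is named.

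*Covariates are commonly left to the SAP.* True of silence, but section 2.14 is not silent. It names specific tests, and those tests have no place for a covariate.

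On synergy, the text says only that it may occur, and no interaction test is planned. That limits the point to which conclusions the design can support.

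**Conclusion.** The point holds in this form. For BMD and blood markers the stated between-arm tests are valid but leave precision unused: 5% to 35% of the variance against a change-score comparison, and 9% to 81% against a final-value comparison, over r from 0.3 to 0.9. These figures assume equal SDs before and after treatment and a correlation that the document does not give.

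The within-arm tests cannot establish efficacy or rank the arms, because every arm is active and the supplements are shared. This follows from the design and needs no assumption about r. The plan should therefore not leave them level with the randomised comparison. Synergy is not estimable from these three arms; showing that the combination beats each single treatment would be equally compatible with simple additivity.

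This is a recommended improvement. It does not mean that the planned between-arm analysis is invalid, and it does not repair the sample size.

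**What to change.** In section 2.14:

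1. State that the between-arm comparison is primary.
2. For BMD and each blood marker, use ANCOVA of the week-12 value on arm and baseline value, with robust standard errors.
3. For SF-MPQ, OSS, MMSE and BDI-II, replace repeated measures ANOVA with a mixed model of the five post-baseline visits, with arm, visit, arm × visit and the baseline score as covariate.
4. Delete the rule that chooses the test by preliminary checks, including the chi-squared wording, in favour of these prespecified models.
5. Report within-arm changes descriptively, with intervals if wished, but without p-values.
6. Limit conclusions to whether the combination is better than each single treatment. Do not conclude that it is synergistic or that any arm is effective in its own right.

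The second primary outcome, the overall effective rate, is a proportion and is not covered by these models. The Bonferroni split over the two primary outcomes is unaffected.

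The cost is analysis wording and narrower claims. The baseline data are already in the schedule, no patient or visit is added, and section 2.16 describes the trial as still recruiting.
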